# Preventing frailty with the support of a home-monitoring and communication platform among older adults—a study protocol for a randomised-controlled pilot study in Sweden

**DOI:** 10.1186/s40814-022-01147-4

**Published:** 2022-08-23

**Keywords:** Fragility, Frailty, Monitoring, Information and Communication Technology, ICT, eHealth, Healthcare, Disability, Prevention

## Abstract

**Background:**

POSITIVE (*i.e. maintaining and imPrOving the intrinSIc capaciTy Involving primary care and caregiVErs*) is a new intervention program consisting of home-monitoring equipment and a communication platform to support treatment of frailty symptoms initially in primary care and prevent disability in older adults.

**Methods:**

The primary objectives are to estimate the potential efficacy of the POSITIVE system on improving frailty in at least one point in Fried’s criteria and five points in Frailty Trait Scale. The secondary objectives are to (A) assess the recruitment, retention, drop-out rates, compliance with the intervention and the intervention mechanisms of impact; (B) evaluate the usability and acceptance of the POSITIVE system, and to get estimations on; (C) the potential efficacy of the intervention on improving the participants’ physical performance, cognitive functions, mood, independency level in activities in daily living, the impact on quality of life and number of falls during the follow-up period; (D) the impact on the caregiver quality of life and caregiver burden; and (E) on the consumption of health care resources, participants’ perception of health and level of care received, and healthcare professionals’ workload and satisfaction.

A randomised controlled, assessor-blinded pilot study design recruiting from a primary care centre in Stockholm Region will be conducted. Fifty older adults identified as pre-frail or frail will be randomised into a control or an intervention group. Both groups will receive a medical review, nutritional recommendations and Vivifrail physical exercise program. The intervention group will receive the POSITIVE-system including a tablet, the POSITIVE application and portable measurement devices. The participants receiving the POSITIVE program will be monitored remotely by a primary care nurse during a 6-month follow-up. Data will be collected at baseline, 3 and 6 months into the intervention though the platform, standardised assessments and surveys. A process evaluation as per Medical Research Council guidance will be conducted after the 6-month follow-up period.

**Discussion:**

The implications of the study are to provide estimations on the potential efficacy of the POSITIVE system in improving frailty among older adults and to provide relevant data to inform powered studies of potential efficacy and effectiveness, as well as to inform about the feasibility of the current study design.

**Trial registration:**

ClinicalTrials.gov. Registration number: NCT04592146. October 19, 2020.

**Supplementary Information:**

The online version contains supplementary material available at 10.1186/s40814-022-01147-4.

## Background

The world population is ageing rapidly. Ageing and age-related diseases pose a challenge for individuals, families as well as for social, economic, and healthcare systems. By 2050, the world population aged 60 years and older is expected to be over 2 billion people, up from 900 million in 2015 [1]. With the ageing process, several physiological changes occur and the risk of developing chronic diseases, disability, and dependency increase. Instead of focusing on the treatment of specific diseases, changes in the health systems are mandatory to prevent functional impairment and focus on guaranteeing healthy ageing [1].

Frailty is a health state defined as a progressive age-related decline in physiological systems that results in decreased reserves of intrinsic capacity, which confers extreme vulnerability to stressors and increases the risk of a range of adverse health outcomes. Frailty focuses on function and not specifically on diseases [2]. To date, several factors have been identified as risks of frailty among the community-dwelling older adults. In general, older age, female gender, low educational level, sedentary lifestyle, obesity, underweight, cognitive impairment, and comorbidities are associated with the development of frailty [3]. The estimated prevalence of frailty among older adults (+65 years) is 7–12% [4]. Frailty status can be assessed through standardised assessment tools, such as Linda Frieds’ Criteria and Frailty Trait Scale (FTS-5) [4, 5], where the first named measure components associated with frailty include unintentional weight loss, self-reported exhaustion, weakness (grip strength), slow walking speed, and low physical activity [4]. Frailty is potentially reversible with early screening and interventions including physical activity, a complete nutritional evaluation, reducing inappropriate drug prescription and preserving emotional vitality [6–11]. According to earlier research, physical exercise in combination with balanced nutrition has the strongest evidence level for positive outcomes in the treatment of frailty symptoms [10, 12].

Several studies have shown that telehealth can be effective in the treatment of different health conditions, and treatments supported by different information and communication technology (ICT) solutions lead to better health outcomes [13–16]. However, there is little knowledge on the impact of ICT-supported interventions in the treatment of frailty symptoms, due to few published studies on the topic [17, 18]. In this study, ICT will be used to prevent and treat frailty through a home-monitoring platform and a communication system between the patient, caregiver and health care personnel in primary care. The development of the new intervention POSITIVE system (i.e. *The Maintaining and imPrOving the intrinSIc capaciTy Involving Primary Care and caregiVErs*) emerged from the increasing need to develop innovative solutions to improve the delivery of health care for older age groups in Europe, but also to improve cost-effectiveness in treatments [19, 20].

The POSITIVE system consists of a set of applications running on mobile devices and involves all relevant actors in the care process: the older adult, his/her informal caregiver and the health care professionals [19]. The professional’s application further includes a communication platform and referral system between primary and specialized care. However, in this pilot study, the system will be adapted to fit the structure of health care delivery in Stockholm Region and will be used in primary care only.

The purpose of the home monitoring system is to collect relevant information of the frailty status, i.e. variables with high predictive power for adverse events including gait speed, power in the lower limbs, and involuntary weight loss [4], that is generated out of the clinical environment. It monitors the most relevant components associated with intrinsic capacity, such as functional level, nutritional- and emotional status of the older adults. By monitoring these components, the home monitoring kit can facilitate early detection of declines in health status [21] and thereby prevent disability and reduce costs in health care.

Through timely medical interventions, a physical exercise programme named Vivifrail (see Additional file 1), which is integrated into the POSITIVE system including several functions, older adults will potentially improve well-being and quality of life, reduce incidence of falls and hospitalisations and increase their feeling of safety in everyday life. The Vivifrail programme has proved to be efficient in improving the health status of older adults [22–24] and is one of the strategies in the European Union (EU) to promote healthy aging. However, in Sweden, the prescription of a physical exercise program targeting different levels of frailty (robust, pre-frail, frail and person with disability) as in Vivifrail, is a new concept. The Vivifrail programme is developed based on the idea that the health of the older adults can be measured according to their functional ability, instead of focusing on the treatment of separate diseases.

This protocol describes the procedures for the pilot study which will be conducted in Sweden as one of the cohorts within a multi-country POSITIVE project in Spain, Poland and Sweden. The protocol is in line with the Standard Protocol Items: Recommendations for Interventional Trials (SPIRIT) guideline [25] (SPIRIT Checklist see Additional file 2).

## Methods

The primary objectives of the study are to assess the potential of the POSITIVE system on improving frailty by at least one point in Fried’s criteria and five points in Frailty Trait Scale-5 (FTS-5). The secondary objectives are (A) to assess the recruitment, retention, drop-out rates, compliance with the intervention as well as the intervention mechanisms of impact; (B) to evaluate the usability and acceptance of the POSITIVE system, and to get estimations on; (C) the efficacy of the intervention on improving the participants’ physical performance, cognitive functions, mood, independency level in activities in daily living (ADL), quality of life and the impact on number of falls during the follow-up period; (D) the impact on the caregiver quality of life and caregiver burden; and (E) on the consumption of health care resources, participants’ perception of health and level of care received and healthcare professionals’ workload and satisfaction.

### Trial design

This is a randomised-controlled, single-blinded and prospective pilot study. The study processes are presented Fig. 1. Within the protocol, a process evaluation is scheduled and will be conducted in line with Medical Research Council (MRC) guidance for process evaluations. The components in the evaluation will follow the guidelines regarding the context, implementation level activities and mechanism of impact, such as participant’s responses to and interactions with the interventions [26].

**Fig. 1 Fig1:**
[figure not shown]
POSITIVE pilot study CONSORT-style flowchart

### Study setting

This pilot study will be conducted at one primary care centre (PCC) at the Stockholm Region. In Sweden, the responsibility for delivering health care services is divided between the government, regions, and municipalities, and is for the most part funded by tax revenues. Municipalities have the responsibility for provision of older adults and primary care. Further, the basic care for all age groups is delivered by primary care. For care that requires specialist treatment and/or further investigation, primary care can refer patients to specialised care [27]. In the Stockholm Region, health care interventions to older adults can also be delivered in geriatric public or private in- and outpatient units, which specialise in acute and chronic conditions due to ageing. However, most patients who are treated in geriatric care are older adults with health conditions requiring acute interventions [20].

### Patient and public involvement

The POSITIVE-system has been developed using a user-centred design [28] including walk-throughs and testing demos among voluntary older adults in Spain and Sweden. These activities have proved to be crucial in the development of the system’s technical functions and user-friendliness. The results of the study will be disseminated to the study participants through the PCC.

### Sample size and power considerations

A sample size calculation is not required for feasibility and pilot studies [29, 30]. However, the sample needs to represent the target population and to be large enough to indicate the possible outcome of the intervention [31]. This study will recruit 50 participants, 25 in the control group (CG) and 25 in the intervention group (IG).

### Participants

The eligibility/exclusion criteria for study participation can be seen in Table 1.

**Table 1 Tab1:** Eligibility and exclusion criteria

Eligibility criteria	Exclusion criteria
• Age ≥ 70 • Living at home • Having a caregiver/relative and/or supervision at home, or by a friend or partner, not necessarily living in the same building • Barthel Index ≥ 90 [29] • Have at least 1 criterion from Fried’s criteria	• Inadequate home infrastructure to host the required technology • Inability to understand how to use the POSITIVE system • Diseases that may affect prescription therapy: acute myocardial infarction in the last 3 months, unstable angina, aortic dissection, severe aortic stenosis, endocarditis/acute pericarditis, acute thromboembolic disease, acute heart failure, orthostatic hypotension (uncontrolled), recent fracture in the last month, terminal disease (< 12 months of life expectancy), other pathologies involving clinical instability • Psychiatric disorders that may potentially interfere in the clinical trial • History of alcohol/drugs abuse • Living with another participant, • Participating in other clinical studies • Three or more hospitalisations in the last year

To determine whether a participant can or cannot understand the use of the POSITIVE system, the participant will be asked to open the POSITIVE application in a tablet. Then the assessor will ask the participant to open different functions in the application and describe what they see. The caregivers’ and the health care workers’ perspectives on the POSITIVE system will be considered, and they will also be included as study participants.

### Participant timeline

Participant enrolment in Sweden started in November 2020, and the last follow-up is scheduled for October 2021. Time schedule for enrolment, interventions and assessments are shown in Fig. 2.

**Fig. 2 Fig2:**
[figure not shown]
Schedule for enrolment, interventions and assessments. t-1, before allocation; t0, allocated; t1, baseline; t2, week 2; t3, week 12; t4, week 24; t5, post-follow-up. MNA-S, Mini Nutritional Assessment Short Version; SPPB, Short Physical Performance Battery; Whodas, World Health Organization Disability Assessment Schedule; MoCA, Montreal Cognitive Assessment; GDS-S, Geriatric Depression Scale Swedish Version; EQ-5D-5L, EuroQol- 5D-5L; HCRS, Health Care resources consumption; QSOM, Questionnaire on the Organisational Model; Acceptability questionnaires, Acceptability QS; SUS, System Usability Scale; UEQS, User Experience Questionnaire

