### Recruitment

A nurse at the PCC will pre-screen potential study participants from an electronic patient register system according to age and the excluding medical conditions. After identification, the nurse will send letters to potential participants, including an invitation to participate in the study. The potential participants will be asked to answer whether they are interested in taking part either by calling a contact number, answering through a letter or sending an e-mail. Posters and brochures about the study will be placed at the PCC and clinical staff will be asked to inform any potential older adult about the study. After receiving contact information for potential participants, a research assistant will call to inform them about the project and go through the eligibility criteria. If the participant meets the criteria, the research assistant will book a time for a home-visit. In this visit, the research assistant will provide oral and written information about the study and will ask for written consent. If the participant will meet all the eligibility criteria, and will obtain the written consent, he/she will be enrolled in the POSITIVE study. After the participant is enrolled, she/he will be randomised into the study.

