### Interventions

#### Multimodal interventions

The participants will be randomised into one of the two groups and the interventions will be delivered in the participants’ homes. The duration of the intervention period is 6 months, at baseline, after 3 and 6 months into the intervention for both the control (CG) and the intervention group (IG). The time schedule for the study interventions is shown in Fig. 2.

Both the CG and the IG will receive a medical review via the PCC to ensure that the study participants follow appropriate medication. Furthermore, all participants will receive generic nutritional recommendations and physical exercise program according to the Vivifrail prescription guide [34]. Since the abovementioned interventions have evidence in improving frailty status [6–11], both treatment arms will receive these interventions, and this study can focus on the evaluation of the impact of using the POSITIVE technical solution to support the intervention.

The Vivifrail program is divided into six different exercise program levels, according to different functional levels and level of frailty, and possible risk of falls. The exercises include cardio exercise such as walking, strength and balance exercises and stretching. All participants will receive a program which is prescribed according to their functional level. In terms of improvement in the condition, a participant can continue to follow Vivifrail program according to a higher functional level or the program for robust persons until the end of the study. The programs and recommendations will be introduced and handed out by the research assistant at baseline. All participants will have the opportunity to call a physiotherapist in case they have questions or doubts considering the training according to Vivifrail. Furthermore, they can visit the PCC whenever they need during the follow-up, as a part of the standard care.

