### Data collection

A technical researcher from KTH will collect data received from the POSITIVE platform. The server for the POSITIVE platform will be provided by Amazon Web Services. This service meets General Data Protection Regulation (GDPR) requirements [35] in terms of security and encryption of personal data, ability to restore the availability and access to personal data in a timely manner in the event of a physical or technical incidence. It also meets requirements for regularly testing, assessing and evaluating the effectiveness of technical and organizational measures for ensuring the security of processing. Further, the technology and methodology in the pilot meets security requirements, since pseudonymized data will be used. The pilot complies with the International Organization for Standardization (ISO) 27001 standards on information management security, and Hypertext Transfer Protocol Secure (HTTPS) is used for all connections.

The data collection in the periodic follow-ups will be conducted by a blinded research assistant. The data collection flow is shown in Fig. 1. The research assistant will write field notes after each contact with the participant to describe and understand the context.

The quantitative and qualitative data from the older adults and caregivers will be collected partly during home visits and partly through phone calls. Data from the informal caregivers will be collected through posted surveys if the caregivers do not live in the same household. Demographics from the participants and their caregivers, which will be collected consists of background data (age, comorbidities, type of housing, relationship to the older adult, employment, etc.). The participants’ health care resource consumption and their overall level or physical activity will be assessed at baseline, 3 and 6 months into the intervention (See Fig. 2).

Data collected from health care professionals will be collected through surveys and qualitative interviews at 2 weeks, 3 and 6 months into the intervention. The surveys consist of background data (age, education, number of working years, etc.) and structured questionnaires. The interviews will be conducted by a researcher focusing on the use of technology and the implementation processes.

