## Discussion

The implications of the study are to provide estimations on the efficacy of the POSITIVE system in reducing frailty symptoms among older adults, prevent disability and dependency, as well as to affect several other health-related domains. Further, the study will contribute knowledge about the feasibility of the current study design in Sweden, perceived value of the POSITIVE system, its utility and the acceptability of the POSITIVE system among the different stakeholders. Thus, the study will give relevant data to inform powered studies of efficacy and effectiveness.

Our primary objective relates to improving frailty in at least one criterion. The multicomponent intervention addresses frailty as a clinical entity, measured with the Linda Fried’s criteria and with FTS-5. The multicomponent intervention we administer is known to be effective, but we are also exploring whether the support of our technology boots its effect. The two frailty scales have common items, such as grip strength, gait speed and level of physical activity, and we do not expect to see great differences between the scales. In the case we find any differences during the data analysis, we will discuss the possible effects of the intervention on the items that are not repeated, including weight loss and exhaustion in the case of the Fried’s scale, and balance and body mass index in the case of the FTS-5. Further, we will discuss the suitability of the different assessment tools to be used in future powered studies.

Limitations in this study include the challenges in blinding the assessor, since the study is not blinded for the participants, and they may reveal their allocated group to the assessor. However, the participants will be reminded in all contacts with the assessor not to reveal whether they are using the POSITIVE system or not. Another limitation is that the selection process of the participants will not be randomised, but the potential participants will be invited to contact the research group voluntarily if they are interested in the study. This fact may lead to selection bias considering that the study participants may not provide a heterogenous and representative sample of the older adult population in Sweden.

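### The Fig. 2 caption puts baseline after allocation in a trial where participants know their arm, and the text does not say which Fried and FTS-5 values are the reference for improvement

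*Protocol article*

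**What the plan says.** **Order of events.** The caption of Fig. 2 (Participant timeline) defines the time points as "t-1, before allocation; t0, allocated; t1, baseline; t2, week 2; t3, week 12; t4, week 24". It has a separate time point before allocation and still lists baseline after allocation. The Recruitment section describes a telephone call, a home visit with consent and an eligibility check, and enrolment. It then says: "After the participant is enrolled, she/he will be randomised into the study". No baseline battery is mentioned before that step. The Multimodal interventions section places baseline within the intervention period and says: "The programs and recommendations will be introduced and handed out by the research assistant at baseline".

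**Blinding.** The abstract calls the design assessor-blinded: "A randomised controlled, assessor-blinded pilot study design recruiting from a primary care centre in Stockholm Region will be conducted". Trial design says: "This is a randomised-controlled, single-blinded and prospective pilot study". The Data collection section says who collects data blind: "The data collection in the periodic follow-ups will be conducted by a blinded research assistant". The Discussion concedes that participants are not blinded and may disclose their group. As a safeguard, "the participants will be reminded in all contacts with the assessor not to reveal whether they are using the POSITIVE system or not".

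**What the reference value is for.** The objectives in Methods ask for an improvement of at least one point on Fried's criteria and five points on FTS-5. Table 1 makes at least one Fried criterion a condition of entry.

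**The concern.** A reference value fixed before allocation cannot be affected by allocation. One taken afterwards can, if the participant or the assessor knows the arm. Blinding the assessor closes only part of that route, because the participant still answers the questions and performs the tests.

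The Background lists self-reported exhaustion among Fried's components, along with grip strength and walking speed, which depend on effort. The Discussion says that grip strength, gait speed and physical activity are shared with FTS-5, and that FTS-5 adds balance and body mass index. Of these, body mass index is hard to influence; the others are less protected.

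At stake is the estimate of improvement on the two primary scales. The article intends that estimate, and the study design, to inform later powered trials, so a flaw in the visit order could be carried forward.

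**Working it through.** The plan gives no effect size, standard deviation or power, so there is no figure of its own to reproduce beyond 25 + 25 = 50. The check is mainly a comparison of passages.

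1. **Is baseline after allocation?** By the Fig. 2 caption, yes: t0 is allocation and t1 is baseline. Recruitment fits this order, since randomisation follows enrolment with no baseline assessment in between.
2. **Is there a Fried value before allocation?** There must be some Fried assessment. Table 1 requires at least one criterion, and randomisation follows the eligibility check. The rule needs only one criterion to be met, so it does not by itself guarantee a recorded full score.
3. **Is that value the reference?** Not stated. The article does not say whether Fried's criteria are repeated at t1 or which value enters the analysis.
4. **Is there an FTS-5 value before allocation?** None is stated. FTS-5 is not an eligibility criterion.
5. **Who might know the arm at t1?** The participant, by the Discussion. The assessor, if the participant discloses it, which the Discussion also allows for.
6. **What cannot be checked?** Which instruments fall at t-1 and which at t1, because the body of Fig. 2 is not shown.

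**Illustration of sensitivity, not an estimate.** Assume 25 per arm, the stated one-sided 0.05, no true effect, an analysis of change from baseline, and an arm-related baseline error of d standard deviations of the change score in favour of the intervention. By the normal approximation the false-positive rate is Φ(d × √(25/2) − 1.645), with √12.5 = 3.536.

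| d (assumed) | Argument of Φ | False-positive rate |
|---|---|---|
| 0 | −1.645 | 0.05 |
| 0.10 | 0.354 − 1.645 = −1.291 | 0.098 |
| 0.25 | 0.884 − 1.645 = −0.761 | 0.223 |
| 0.50 | 1.768 − 1.645 = 0.123 | 0.549 |

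An error in the other direction works against the intervention. For d = −0.10 the rate is Φ(−0.354 − 1.645) = Φ(−1.999), about 0.02, and a real effect would be masked to the same degree.

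For a responder analysis, assume a control rate p0 and a spurious excess s, with p1 = p0 + s and p̄ their mean. The rate is Φ{[s − 1.645 × √(2p̄(1 − p̄)/25)] / √[(p1(1 − p1) + p0(1 − p0))/25]}. With p0 = 0.40 and s = 0.10 this is Φ[(0.100 − 1.645 × 0.1407)/0.140] = Φ(−0.939), about 0.174. Over p0 from 0.30 to 0.50, s of 0.05, 0.10 and 0.15 gives about 0.10, 0.17 to 0.18, and 0.28 to 0.29.

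The document gives none of d, s or p0.

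**The case against.** The strongest reply is that the deciding evidence is not visible. Only the caption of Fig. 2 can be read, and baseline may partly label the start of the intervention, since the programmes are handed out then. Both frailty scales may in fact be measured at t-1. This stands as a limit on certainty. It does not remove the point, because in that case the caption misdescribes the order and the reference value is still unnamed.

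Four stronger readings are tempting, and the article does not support them.

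- **That blinding is promised only for the follow-ups.** The abstract and Trial design state assessor blinding without limit, and the reminder in the Discussion covers all contacts with the assessor. The Data collection sentence does not say that the baseline assessor is unblinded.
- **That the hand-out at baseline reveals the arm.** The exercise programme and nutritional recommendations go to both groups. The POSITIVE system is installed by a separate technical researcher, and allocation is done by someone outside screening.
- **That the whole primary reference is compromised.** A Fried assessment has to precede allocation and may be the reference.
- **That people who leave between allocation and t1 are a further loss that an earlier baseline would recover.** They would ordinarily have no follow-up outcome either, so moving the baseline would recover little.

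It is also fair to say that a baseline error need not pass in full into the result. The Data analysis section specifies linear and logistic mixed models without saying how baseline enters. The full transfer shown above belongs to a change score; a model with baseline as a covariate would pass on only part of it. Finally, the Discussion already acknowledges that participants are unblinded, but its safeguard addresses disclosure to the assessor, not the participant's own knowledge.

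**Conclusion.** The point holds in limited form. The stated order puts baseline after allocation in a trial where participants know their arm, and the article does not identify the reference value for either primary scale. The exposure is clear for FTS-5 as the text stands, because no measurement before allocation is stated. For Fried's criteria it exists only if they are repeated at t1 and the repeat is used.

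The size is unknown. The calculations show that with 25 per arm even a modest arm-related error would matter to a one-sided 0.05 test, but the error sizes and response rates are assumed, and neither the direction nor the occurrence of the error can be inferred from the article. A reader should not take any particular responder shift as expected. The conclusion also assumes that the caption gives the true order, which the missing figure body prevents confirming. Confidence is medium. The change is worth making because it removes this source of bias at little cost.

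**What to change.** - Complete Fried's criteria and FTS-5, and preferably the rest of the baseline battery, at the existing home visit before allocation.
- Release the allocation only after these values are recorded.
- Name them as the baseline values in the analysis of both primary outcomes.
- Align the t-1, t0 and t1 labels in Fig. 2 and its caption with that order.
- If the scales are already taken before allocation, correct the caption and say so in the text.

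The cost is a longer assessment for a few people who are then found ineligible. The article does not say how much of the battery fits into the consent visit. If time is short, the two frailty scales come first, since the primary thresholds depend on them.
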